### Statistical methods

The primary objective of the study is to demonstrate the equivalency between total exposure and trough levels of both Prograf^®^ and Envarsus^®^ (with a daily dose conversion factor of 0.7) in compliant patients without any protocol deviations. Therefore, the primary endpoint is the full AUC0-24 of tacrolimus levels over 24 hours. The objective is to demonstrate that the 90% confidence interval for the ratio of the full AUC0-24 of Envarsus^®^ (with a conversion factor of 0.7 for the daily dose) to Prograf^®^ is within the acceptance interval of 0.8 - 1.25 (33). This interval has been chosen in accordance with the German Federal Institute for Drugs and Medical Devices. As a secondary analysis, whether the confidence interval is also within the narrower interval of 0.9 to 1.11 recommended for drugs with a narrow therapeutic index (NTI) will be checked (33).

Demographic and baseline characteristics will be summarized as absolute and relative frequencies (for categorical outcomes), median and interquartile ranges (IQR), or arithmetic means and standard deviation. Pharmacokinetic measures will be summarized as median, geometric mean, arithmetic mean and standard deviation, minimum and maximum, and coefficient of variation. The primary endpoint – full AUC0-24 – will be calculated from tacrolimus measurements after administration of the respective medication by linear interpolation between measurement time points (see **Supplementary Material**). It will then be analyzed using an ANOVA model on the log-transformed AUC0-24 values comparing Prograf^®^ and Envarsus^®^ with sequence, subject within sequence, and period as further fixed factors as suggested by the EMA guideline (33). A summary of the assessment of the primary objective in terms of the estimand framework is given in the **Supplementary Material**.

In addition to full AUC0-24 analysis, the following pharmacokinetic parameters will form part of the evaluation: C_0_, C_max_, t_max_, and their corresponding coefficients of variation. Pharmacokinetic half-life and apparent clearance after oral administration of Envarsus^®^ and Prograf^®^ will be evaluated accordingly. Pearson’s correlation coefficients will be used to assess suitability and trough levels and AUC0-24 will be correlated.

Low NFAT expression indicates high immunosuppression and high NFAT expression indicates low immunosuppression. The tacrolimus effect is therefore complementary to the NFAT transcripts (E=1-NFAT%). The residual NFAT expression at each time point will be compared to the corresponding tacrolimus blood concentration to estimate the peak (E_peak_) and trough (E_trough_) effect. With the help of the sigmoid E_max_ model, the immunosuppressive effect will be estimated as the percentage of E_max_ (E=%E_max_).

A test for univariate associations between changes in the gut microbial abundance profile will be performed during the switch from Prograf^®^ to Envarsus^®^ compared to changes during the pre- and post-switch time intervals (Wilcoxon test). We will also include Prograf^®^ AUC0-24 and *CYP3A* genotypes as additional predictors in these models to quantify whether microbial AUC0-24 predictors are consistent or different between Prograf^®^ and Envarsus^®^ AUC0-24 and the extent to which gut bacterial drug metabolism is independent of host metabolism. We will attempt to identify gut microbial correlates of adverse events and rejection, but the analyses will be exploratory.

All persons performing the analyses will be blinded to the sequence order. The statistical analysis plan, in which all planned analyses are described in detail, is finalized before the database lock.

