Data on the pharmacokinetics of immediate-release tacrolimus versus prolonged-release tacrolimus in the pediatric population are scarce and not available for immediate-release tacrolimus versus extended-release LCT-tacrolimus. Vondrak et al. showed a 1.3 to 1.9 increase in tacrolimus Tmax for prolonged-release tacrolimus versus immediate-release tacrolimus in pediatric solid organ transplant recipients (9). The main finding of this study was that systemic exposure (AUC0-24) was lower for the early post‐transplant period for the prolonged‐release formulation which equalized by 1 month after transplantation. These findings were consistent with those reported in *de novo* adult transplant recipients (9, 10). In adult transplant recipients, the switch from immediate-release tacrolimus to extended-release LCPT tacrolimus was safe and resulted in a 12.5% to 16% increase in the tacrolimus trough level over total daily dose ratio, indicating improved bioavailability (11, 12). Despite the finding that tacrolimus trough levels remained within the standard reference range for most patients (11), the coefficient of variation for the intra-patient variability did not change significantly after the switch from immediate-release tacrolimus to extended-release LCP tacrolimus (13).

The objective of this study is to evaluate the pharmacokinetic profile, efficacy, and tolerability of Envarsus^®^ in children and adolescents aged ≥ 8 and ≤ 18 years to assess its potential role as an additional option for immunosuppressive therapy after pediatric kidney transplantation.

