### Study drugs

#### Prograf^®^ and Envarsus

Prograf^®^ and Envarsus^®^ contain the active ingredient tacrolimus. Tacrolimus is an immunosuppressive drug that reduces T-cell activity by binding to a cytosolic protein (FKBP12); it specifically and competitively inhibits calcineurin, leading to a calcium-dependent inhibition of T-cell signaling pathways (14, 15).

Prograf^®^, the immediate-release formulation of tacrolimus, exhibits significant inter- and intra-individual variability in absorption due to interactions with food and concomitant medications and the cytochrome P-450 system, which is subject to functional polymorphisms. In addition, Prograf^®^ has rather low bioavailability due to poor water solubility and pre-systemic gastrointestinal metabolism (16, 17). In humans, tacrolimus has been shown to be absorbed throughout the gastrointestinal tract. Available tacrolimus is generally absorbed rapidly.

Envarsus^®^ is a prolonged-release formulation of tacrolimus and was approved by the European Medicines Agency (EMA) in 2014. It is currently indicated for the prophylaxis of transplant rejection in adult kidney or liver allograft recipients and treatment of allograft rejection in adult patients refractory to other immunosuppressive drugs but, to date and in contrast to Prograf^®^, it has not been officially licensed for use in children. The prolonged-release formulation results in an extended oral absorption profile with an average time to maximum blood concentration (C_max_) of approximately 6 hours (t_max_) at a steady state. The oral bioavailability of Envarsus^®^ is approximately 40% higher than the same dose of the immediate-release tacrolimus formulation Prograf^®^ in kidney transplant patients (18). There is a strong correlation between AUC0-24 and steady-state whole blood trough levels for Envarsus^®^. Therefore, monitoring of whole blood trough levels provides a good estimate of systemic exposure (19).

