^2d^Full AUC0-240-240-24: Patients need to be hospitalized for the sampling of blood (9.5 ml whole blood per patient) to determine tacrolimus levels; time = 0 is defined as 12 hours after the last intake of Prograf^©^/24 hours after the last intake of Envarsus^©^. Pharmacokinetic Analysis: 0.5 ml whole blood (EDTA) per sampling point (0.0, 1.5, 2.0, 4.0, 6.0, 8.0, 12.0, 13.5, 14.0, 16.0, 20.0, and 24.0 h) to be stored at -20° C until shipping (to be shipped frozen to Cologne, Labor für Therapeutisches Drug Monitoring. Pharmacodynamic Analysis: 0.5 ml whole blood (lithium-heparin) per sampling point (0.0, 1.5, 2.0, 4.0, 6.0, 20.0, and 24.0 h) to be stored at room temperature and to be shipped later the same day to Heidelberg Institute of Human Genetics.

^2e^Pharmacogenetic Analysis: At baseline visit 1 ml whole blood (EDTA) for pharmacogenetic analysis (to be shipped at room temperature.

^2f^Trough (C_0_) levels: defined as 12 hours after the last intake of Prograf^©^/24 hours after the last intake of Envarsus^©^. 0.5 ml whole blood (EDTA) to be stored at -20° C until shipping (to be shipped frozen).

^2g^Microbiome Analysis: fecal samples: metagenomic-/transcriptomic analysis and metabolomics; urine and blood samples: metabolomics.

^3^In phase 3b, patients will be switched to the other immunosuppressant for 4 weeks.

^4^Patients must return the unused Envarsus^®^ for accountability and destruction of unused tablets at Visit 3a for Group A and also at Visit 4 for Group B.

^5^The adverse event documentation period for this trial begins with informed consent and ends with the last study visit.

^6^Patient hospitalizations must happen from Monday to Wednesday as samples for pharmacodynamic analysis must be shipped immediately within 1 day and must reach the central lab in Heidelberg on Thursday at the latest.

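### Pearson's correlation, the tool named for judging suitability, would not reveal that equal troughs correspond to different AUC0-24 on Prograf and Envarsus

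*Protocol article*

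**What the plan says.** The sentence at issue closes the pharmacokinetic part of Statistical methods in the protocol article: Pearson's "correlation coefficients will be used to assess suitability and trough levels and AUC0-24 will be correlated". It does not define suitability, set a value of r that would count as adequate, or say whether the coefficient is computed by formulation or across both.

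The subsection on Prograf and Envarsus under Study drugs shows how the authors use such a result. It states: "There is a strong correlation between AUC0-24 and steady-state whole blood trough levels for Envarsus". From this it infers that "monitoring of whole blood trough levels provides a good estimate of systemic exposure".

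Three other statements bear on the point:

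- Trough is "defined as 12 hours after the last intake of Prograf^©^/24 hours after the last intake of Envarsus" (Table 2 footnotes, Study assessments), so C0 sits at a different place in the dosing interval for each drug.
- Oral bioavailability of Envarsus "is approximately 40% higher than the same dose of the immediate-release tacrolimus formulation" (Study drugs).
- In adults, the switch gave a "12.5% to 16% increase in the tacrolimus trough level over total daily dose ratio" (Introduction).

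The article also plans the AUC0-24 ratio with a 90% CI as the primary analysis, an evaluation of C0 among the pharmacokinetic parameters, and a comparison of trough levels between formulations as a secondary objective.

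**The concern.** The Introduction says that tacrolimus dosing is guided by trough. In a crossover of two formulations, the useful question is therefore not only whether trough rises with AUC within each formulation. It is also whether a given trough stands for the same AUC on both, and how closely AUC can be predicted from it. With C0 taken at 12 hours for one drug and 24 hours for the other, an identical relation cannot be assumed.

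Pearson's r addresses neither matter. The trial could report strong correlations for both formulations and call trough suitable, as the background already does for Envarsus, while the formulations differ in AUC at equal trough. At stake is a secondary conclusion about the use of trough, not the bioequivalence result.

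**Working it through.** The documents state no correlation, threshold or formulation gap for trough and AUC, so there is no figure of the plan to reproduce.

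**1. Does r respond to a gap within a formulation?** For any constant k > 0, corr(C0, k·AUC) = corr(C0, AUC). A numerical check with 27 simulated pairs gave r = 0.8804 with AUC multiplied by 1, 1.21, 1.24 or 2.

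**2. How large might a gap be? (illustration only)** Inputs are relative bioavailability of about 1.40 and trough per dose of 1.125 to 1.16.

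- Gap in AUC/C0 = 1.40/1.16 = 1.207 to 1.40/1.125 = 1.244.
- Using the Sample size section's expected AUC ratio (0.9749) and the conversion factor (0.7) instead: 0.9749/0.7 = 1.393, giving 1.393/1.16 = 1.201 to 1.393/1.125 = 1.238.
- At factor 0.7, the first pair of inputs corresponds to an AUC ratio of 0.7 × 1.40 = 0.98 with a trough ratio of 0.7 × 1.125 = 0.79 to 0.7 × 1.16 = 0.81.

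The inputs come from different cited studies. The article's claim of a reduced peak-to-trough profile could point the other way, since a flatter curve has a higher trough for the same AUC.

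**3. What would r show under such a gap?** Simulation with 27 patients and 1,500 runs; medians are shown. Assumptions: between-patient log-SD 0.3-0.5, within-patient log-SD 0.2, and residual log-SD of trough given AUC 0.10-0.25.

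| Between-patient SD | Residual SD | r by formulation | Pooled r, no gap | Pooled r, gap 1.21 | Pooled r, gap 1.24 |
|---|---|---|---|---|---|
| 0.3 | 0.10 | 0.96 | 0.962 | 0.929 | 0.922 |
| 0.3 | 0.20 | 0.87 | 0.865 | 0.840 | 0.837 |
| 0.4 | 0.15 | 0.95 | 0.942 | 0.922 | 0.916 |
| 0.4 | 0.25 | 0.87 | 0.858 | 0.844 | 0.842 |
| 0.5 | 0.25 | 0.90 | 0.892 | 0.880 | 0.877 |

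By formulation, r is the same with or without the gap. Even if the formulations were pooled, which the article does not say, r would fall by only about 0.01-0.04 over the whole grid. The second and fourth rows give the same r (0.87) with residual SDs of 0.20 and 0.25. The wider exposure range offsets the poorer prediction, so r is not a measure of prediction error.

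**4. What do the planned summaries add?** With complete pairs, the geometric mean ratio of AUC/C0 equals the AUC ratio divided by the C0 ratio, so a point estimate follows from planned outputs. Its CI does not. Writing d for the within-patient log difference, Var(d_AUC − d_C0) = Var(d_AUC) + Var(d_C0) − 2 Cov(d_AUC, d_C0), and separate summaries do not supply the covariance.

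**5. What would the direct comparison deliver?** n = 27 (Sample size section), SE = SD × √(2/27), df = 25, t(0.95) = 1.708. Residuals are assumed independent between a patient's two periods. Power is for a two-sided 5% test.

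| Residual log-SD | 90% CI factor | Power at 1.207 | Power at 1.244 |
|---|---|---|---|
| 0.10 | 1.048 | >99% | >99% |
| 0.15 | 1.072 | >99% | >99% |
| 0.20 | 1.097 | 91% | 97% |
| 0.25 | 1.123 | 76% | 87% |

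Example at SD 0.25: SE = 0.25 × 0.272 = 0.068, and exp(1.708 × 0.068) = 1.12. An observed ratio of 1.207 would have a 90% CI of about 1.07-1.36.

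**The case against.** The strongest reply is that the article never claims to test whether one trough value means the same AUC on both drugs. Its nearest context concerns Envarsus alone, where the question is whether trough tracks exposure, and correlation by formulation is a conventional answer to that. This stands as far as it goes, and r should stay as a description. But the article moves from correlation to trough being a good estimate of exposure, and r does not measure how good an estimate is.

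Second, a gap would not be invisible, because AUC and C0 are each evaluated on both formulations and troughs are compared. This also stands for the point estimate. It does not provide a CI, a comparison of slopes or a prediction error.

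Third, the article says that all planned analyses are described in detail in the SAP, which is not at hand and may contain more. That is why the point is limited to the method the article itself names for this purpose.

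Three stronger readings are tempting and should be resisted:

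- A reader might infer that the protocol shows a 21-24% gap. It does not. The figure divides results from different cited studies, the trough figure is from adults, and the Introduction reads that figure as a sign of improved bioavailability. The 1.25 limit is also no yardstick here, since it applies to the AUC ratio and not to AUC/C0.
- A reader might infer that a gap could pass a suitability test. No threshold or decision rule is stated, so there is no test to pass.
- A reader might infer that dependent pairs will be pooled. The article does not say so, and the plural coefficients are compatible with one per formulation.

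**Conclusion.** The concern holds in limited form. Pearson's r is a fair description of whether trough tracks AUC0-24 within a formulation. It is the wrong instrument for concluding that trough is suitable across formulations, because it is blind to a constant difference in AUC per unit trough, varies with the exposure range sampled and carries no prediction error. The first of these follows from algebra and needs no assumption.

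The size and direction of any real gap are unknown from the documents; 1.21-1.24 is an illustration. The correlation and power figures rest on assumed SDs, and power falls to 76-87% at the top of the range considered. This is an improvement to a secondary analysis that should be made. It does not touch the primary endpoint, the sample size or the data collected.

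**What to change.** In the SAP, before database lock:

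1. State what suitability refers to, and report r separately for each formulation as descriptive only.
2. Assess suitability with the within-patient Envarsus/Prograf ratio of AUC0-24/C0 and its 90% CI, using log(AUC0-24/C0) as the outcome in the same crossover ANOVA as the primary endpoint. The time-zero sample of each 24-hour profile already supplies C0.
3. Report the prediction error of AUC0-24 from C0 for each formulation, for example from a regression of log AUC0-24 on log C0 with a formulation term and patient as a random effect. A formulation-by-log C0 interaction can be added to compare slopes.

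The cost is a few lines of text and one more secondary table. No additional patients, visits or samples are needed.

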## Discussion

Non-adherence to immunosuppressive therapy, particularly in adolescents, can lead to the development of T-cell-mediated and/or antibody-mediated rejections after kidney transplantation, which is the major cause of long-term graft loss.

Once-daily prolonged-release formulation Envarsus^®^ has the potential to improve adherence but is not currently approved for use in adolescents under 18 years of age. Pro-Tac, our multi-center interventional trial, will test the hypothesis that once-daily prolonged-release tacrolimus (Envarsus^®^) is equivalent to intermediate-release tacrolimus and may result in improved drug adherence, a more consistent pharmacokinetic profile, and reduced peak-to-trough after kidney transplantation compared to twice-daily immediate-release tacrolimus formulation (Prograf^®^). This novel concept may optimize immunosuppressive therapy for more stable graft function and improved graft survival.

### Ethics and dissemination

This trial is being conducted in accordance with the German Drug Law (AMG), the German Good Clinical Practice (GCP-V), the International Conference on Harmonization (ICH), GCP guidelines, and other applicable ethical and regulatory requirements. A favorable assessment from the International Electrotechnical Commission (IEC) and approval from the National Competent Authority (NCA) were obtained before the start of the trial. The trial has received a positive primary ethics opinion from the Ethics Committee of the University Hospital of Essen (21-10167-AF) and positive secondary ethics judgments from the Ethics Committees of the University Hospitals of Heidelberg, Hamburg, Cologne, and Essen.

Informed consent is obtained from all participating patients and their parents. Monitoring, audits, and inspections are performed for reasons of quality assurance and to verify that the study is conducted according to the protocol as well as to legal and regulatory requirements applicable to clinical trials.

The study is registered under EUDRA-CT 2019-003710-13 and ClinicalTrial.gov Identifier: NCT06057545.

The results of the study are planned to be published in a Pubmed listed open-source publication.

### Trial status

The first patient was enrolled on 25th April 2023. To date (September 2023), four patients have been enrolled in Essen, Cologne, and Heidelberg.

## Ethics statement

The studies involving humans were approved by Ethics committee of the Medical Faculty of the University of Duisburg-Essen. The studies were conducted in accordance with the local legislation and institutional requirements. Written informed consent for participation in this study was provided by the participants’ legal guardians/next of kin.

## Glossary

**Table d98e2601:**

AMG	German Drug Law
ALT	alanine aminotransferase
AUC0-24	area under the curve
C_0_	trough level
CK	creatine kinase
CKiD	Chronic Kidney Disease in Children
C_max_	maximum blood concentration
CNI	calcineurin inhibitor
CRP	C-reactive protein
DSA	donor-specific antibodies
EMBL	European Molecular Biology Laboratory
e.g.	exempli gratia
eGFR	estimated glomerular filtration rate
EMA	European Medicines Agency
E_peak_	estimate the peak of the blood concentration
E_trough_	estimate trough level
FPFV	first patient first visit
GCP	Good Clinical Practice
yGT	gamma-glutamyl transferase
h	hours
HbA1c	hemoglobin A1c
HLA	human leukocyte antigen
ICH	International Conference on Harmonisation
IEC	International Electrotechnical Commission
IL-2	interleukin 2
IQR	interquartile range
LDH	lactate dehydrogenase
LPLV	Last patient last visit
NCA	National Competent Authority
NFAT	nuclear factor of activated T-cells
t_max_	time to peak drug concentration
